*Aim 1: To evaluate the effectiveness of community health worker delivered Little Holy One on parent and child behavioral and mental health outcomes, using a randomized controlled trial design.* We hypothesize that a) parents in Little Holy One will experience significant decreases in parenting stress and trauma-related symptoms, and significant increases in positive parenting behavior, tribal identity, communal mastery, and b) their children will have lower levels of externalizing and internalizing behavior compared to children in the active control group condition. *Aim 2: To explore the benefit of specific cultural enhancements (promoting tribal identity and communal mastery) of the intervention on parents’ mental health and well-being, by using a single-case experimental design embedded within the randomized controlled trial*. We hypothesize that specific cultural components will increase the impact of Little Holy One by providing immediate and sustained reductions in parental stress after component completion. *Aim 3: Explore how the social network characteristics (*i.e.*, network size, average strength of ties, heterogeneity, density, % same race, % same age, % same gender) of Native American parents are related to both risk for and protection from suicide and opioid use*. Using ego network data, we will extract information about each respondent’s unique network characteristics as correlates of suicide and opioid. *Aim 3a: Examine the impact of the Little Holy One family-based prevention program on the social networks of Native American parents.* We will use pre- and post-intervention data to explore the effect of the intervention on parents’ social networks. *Aim 3b: Determine whether program effects on social networks mediate effects on suicide and opioid among parents*. The effectiveness of behavioral interventions often occur through multiple strategies, the strategies presented in the parent grant remain unchanged, however, we aim to explore the possible efficacy of the Little Holy One program on social networks as levers of change for conferring reduced risk of suicide and opioid use as the group-based nature of the intervention increase social interaction of parents, increases parenting support networks, and is founded in similar values of cultural strengths.

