### Lesson frequency and duration

Participants in the intervention group will be taught the 12 lessons over a 16-week period in individual sessions with their community health worker—a delivery strategy selected to enhance participant engagement, local acceptability, and sustainability [47, 48]. Lessons will be delivered at a location that works best for the participant, including Head Start locations, community centers, or study office space at a convenient time (i.e., after drop-off or pick-up). Participants in the control group will participate in group or individual lessons on nutrition at a convenient time and place for participants. Both the intervention and control lessons will begin 2 weeks after study enrollment, and baseline assessments and randomizations have been completed. Participants in both conditions will be assessed by blinded evaluators using mobile data collection at baseline, 12 weeks (when intervention ends), and 6-, 12-, 18-, and 24-months follow-up. Figure 2 outlines the overall flow of the study below.

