**AIM 3: SOCIAL NETWORKS SUPPLEMENT**										
Caregiver Ego Networks	17	x				x		x		x
Columbia Suicide Severity Rating Scale	6	x				x		x		x

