
Secondary outcomes – Child:The *Strengths and Difficulties Questionnaire* (SDQ) and impact supplement will measure childrens’ externalizing and internalizing behavior via parent report. The SDQ is a 30-item scale which measures 25 attributes on five scales: emotional symptoms, conduct problems, hyperactivity/inattention, peer relationship problems, and prosocial behavior [72].Head Start school attendance will be tracked via teacher report on an ongoing basis for all children enrolled in the study.

***Aim 2****: To explore the benefit of specific cultural enhancements (promoting tribal identity and communal mastery) of the intervention on caregivers’ mental health and well-being, by using a single-case experimental design embedded within the randomized controlled trial*.

Outcomes:Parent stress will be measured using the *Perceived Stress Scale* (PSS). The PSS is a 10-item scale that has been widely used and validated, including in Native American populations [73, 74].Parent communal mastery will be measured using the same 10-item *Communal Mastery Scale* highlighted above [68, 69].Parent tribal identity will be assessed using a modified version of the 6-item *Orthogonal Cultural Identification Scale* as highlighted above [70, 71].

***Aim 3****: Explore how the social network characteristics (*i.e.*, network size, average strength of ties, heterogeneity, density, % same race, % same age, % same gender) of American Indian parents/adult caregivers are related to both risk for and protection from suicide and opioid use*. ***Aim 3a****: Examine the impact of the Little Holy One family-based prevention program on the social networks of Native American parents/adult caregivers.****Aim 3b****: Determine whether program effects on social networks mediate effects on suicide and opioid among parents/caregivers*.

Outcomes:Social networks information will be collected via a 17-item self-report *Caregiver Ego Networks Questionnaire.* Parents will provide information about tribal affiliation, relationships, substance use, communication, parenting support, and cultural involvement of up to 10 of their closest social relationships [75, 76].Suicide risk will be measured with six items from the *Columbia Suicide Severity Rating Scale* (CSSR-S), which has been widely used to identify and assess individuals at risk for suicide across diverse communities and settings [77].

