We will explore the bivariate associations between parent social network characteristics and suicide risk and opioid use. After a foundational understanding of the bivariate relationships is established, we will use generalized linear regression models to investigate the multivariate relationships between individual network characteristics on the outcomes of suicidal behaviors and opioid use. Additionally, we will assess the effect of Little Holy One on individuals’ social networks. The literature continues to support the use of social network measures as predictors of behavioral outcomes yet is less clear when it comes to the role behavioral interventions have on individuals’ social networks [75, 76]. We hypothesize that individuals that are randomized to the intervention group will see a significant positive change in their network composition compared to those in the control arm of the study due to the culturally salient nature of the content of the intervention arm. To assess this, we will use the pre-intervention data and the initial post-intervention data to assess changes in social networks over time between treatment groups.

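### Aim 3a is analysed only as change from baseline to the 12-week network reading, although networks are also collected at 12 and 24 months

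*Protocol article*

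**What the plan says.** All references are to the protocol article.

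- **Objectives, Aim 3a**, names no particular follow-up wave: "We will use pre- and post-intervention data to explore the effect of the intervention on parents’ social networks".
- **Statistical methods, Aim 3**, does name the waves: "we will use the pre-intervention data and the initial post-intervention data to assess changes in social networks over time between treatment groups". The hypothesis stated there concerns the composition of the network.
- **Lesson frequency and duration** places the assessments after baseline at "12 weeks (when intervention ends), and 6-, 12-, 18-, and 24-months follow-up". It spreads the 12 intervention lessons over 16 weeks. **Data collection methods** gives the same 16 weeks, to leave room for make-up sessions.
- **Table 3, Aim 3 rows**: "Caregiver Ego Networks" and "Columbia Suicide Severity Rating Scale" are each marked at baseline, 12 weeks, 12 months and 24 months. The WHO ASSIST row, under Aim 1, carries the same four marks.
- **Objectives, Aim 3b**: "Determine whether program effects on social networks mediate effects on suicide and opioid among parents". The Aim 3 statistical text gives no mediation model and no wave for mediator or outcome.
- **Measures, Aim 3 outcomes**: parents describe "up to 10 of their closest social relationships".

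**The concern.** The Objectives present social networks as a route by which the programme might lower suicide and opioid risk. On that account, what matters is whether networks change and stay changed. A comparison that ends at the first post-intervention reading answers only whether they differ at about the time the lessons stop. If ties form or strengthen more slowly, the analysis would report little effect while the data showing otherwise sit unused. If an early difference fades, the analysis would report an effect without showing that it was short-lived.

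The restriction also stands out within the article. Aims 1 and 2 are analysed with mixed models over repeated assessments, and the same approach is available for networks.

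**Working it through.** There is no figure of the plan to reproduce: Table 4 has no Aim 3 row. The check compares sections of the article and adds two short calculations.

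**1. Waves collected and waves used.** Post-baseline ego-network waves in Table 3: 12 weeks, 12 months, 24 months, so 3. No network data are collected at 6 weeks or 6 months, so the initial post-intervention wave can only be 12 weeks. Waves used in the stated Aim 3a analysis: 1. Unused: 3 − 1 = 2 of 3.

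**2. Timing of the 12-week visit against delivery.** The lessons may take 16 weeks.
- If the 12 weeks run from the first lesson, delivery can end 16 − 12 = 4 weeks after the visit.
- If they run from enrolment, with lessons starting 2 weeks later, the gap can reach 2 + 16 − 12 = 6 weeks.
- If the visit is held whenever the lessons end, as the article's parenthesis could be read, the gap is zero.

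The article does not state the time origin, so early reading is possible rather than certain. Step 1 holds in all three cases.

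**3. What the schedule allows for Aim 3b.** Networks, the suicide scale and the ASSIST share four visits. Taking the ASSIST as the source of opioid use is an assumption; it is the only listed instrument that could supply it. Post-baseline pairs with the network measured before the outcome are:
- network at 12 weeks, outcome at 12 months;
- network at 12 weeks, outcome at 24 months;
- network at 12 months, outcome at 24 months.

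A time-ordered analysis is therefore feasible with the planned data. The only network effect that the article defines is the 12-week change. Pairing it with a 12-week outcome would leave the direction open, and pairing it with a later outcome would not.

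**4. The limit of 10 ties.** For true network size X, the observed mean is E[min(X,10)] = Σ P(X > k), k = 0 to 9. The article gives no distribution of X, so the means below are assumptions. The entries show how much of a true one-tie gain remains visible.

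| Mean size | At limit (Poisson) | Gain visible (Poisson) | Gain visible (negative binomial, size 5) |
|---|---|---|---|
| 3 | 0.1% | 99.6% | 96% |
| 5 | 3% | 94% | 80% |
| 7 | 17% | 78% | 60% |
| 9 | 41% | 52% | 42% |
| 11 | 66% | 29% | 29% |
| 13 | 83% | 14% | 20% |

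The loss runs from almost nothing to most of the gain, and the article cannot say where this population lies.

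**5. Precision at later waves.** For a single-wave comparison of two equal arms with N parents in total (two-sided 5%, 80% power), the detectable standardised difference is d = (1.960 + 0.842) × √(4/N).
- N = 120: 2.802 × √(4/120) = 0.51.
- N = 120 × 0.70 = 84 (30% attrition): 2.802 × √(4/84) = 0.61.
- N = 120 × 0.50 = 60 (50% retention): 2.802 × √(4/60) = 0.72.

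The 24-month section states 50% retention but also 42 per arm. Since 2 × 42 = 84 is 70% of 120, both values of N are shown.

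**The case against.** The strongest defence is that baseline to first follow-up is a reasonable main contrast for an exploratory aim. It is the follow-up least exposed to attrition, and the text does not expressly rule out later waves. An early mediator followed by later outcomes is also sound mediation design, so the 12-week network is not a poor choice in itself. All of this stands, and it is why the 12-week contrast should be kept. It does not remove the point, because the article names the waves for Aim 3a and so leaves two scheduled ones without a stated use.

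Two stronger readings are tempting, and the documents do not support either.

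- A reader might infer that Aim 3b takes mediator and outcome from the same visit, so that mediation has no time order. The article does not say this. It names mediation as an aim and leaves the timing open, which an article may leave to the full plan. The shared waves are what make a lagged analysis possible.
- A reader might infer that the 10-tie list hides network growth. Size is one of seven characteristics listed ("network size, average strength of ties, heterogeneity, density, % same race, % same age, % same gender"), and the stated hypothesis is about composition. The limit does not by itself conceal change in composition, tie strength or density among the named ties, and parenting support is recorded for each of them. Only size is attenuated, and only for parents at or near 10 ties.

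**Conclusion.** The point holds in a limited form. As stated, the Aim 3a analysis uses one of three post-baseline network waves and so can miss later or lasting change. It may also read networks up to 4 weeks before the lessons finish, or 6 if visits are counted from enrolment. That second part assumes that visits keep to a 12-week calendar while some parents use the full 16 weeks.

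For Aim 3b, the supportable request is conditional: if the 12-week network change is the mediator, the outcome should come from a later wave. The 10-tie limit is a caveat on network size, of unknown extent.

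Severity is low. Aim 3 is worded as exploration and labelled a supplement, and no primary or secondary conclusion rests on it.

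**What to change.** In Statistical methods, Aim 3, state that the arm effect on each network characteristic will be estimated in a mixed model using all scheduled waves (baseline, 12 weeks, 12 months and 24 months), with the arm contrast reported at each follow-up wave and the 12-week contrast retained.

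For Aim 3b, state that where the 12-week network change is the mediator, the outcomes are the suicide scale and the ASSIST opioid score at 12 or 24 months, adjusted for baseline network and baseline outcome. The lag gives time order but does not remove confounding between network and outcome, so the result stays exploratory.

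When network size is reported, note the limit of 10 and give the share of parents who reach it at baseline. A new uncapped question is not proposed: recruitment is under way, and parents already enrolled would have no baseline value.

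The cost is analysis work only, with no new visits or items. The price is lower precision at the later waves, as in step 5 of the working. A mixed model keeps parents with incomplete follow-up in the analysis, on the assumption that dropout is explained by the observed data. The lagged mediation analysis will have fewer parents than a 12-week one.

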### Intervention fidelity

To improve quality and adherence to intervention protocols, a session summary form will be completed by interventionists at the conclusion of each intervention/control session documenting what content was covered, how much time the visit lasted, any adverse event reporting or other concerns. All sessions will be audio-recorded and a random 20% will be listened to by the research coordinator on a continuous basis and rated for fidelity. Intervention fidelity is rated on 20 items, on a scale of 1 to 4, with 1 indicating the interventionist did not complete the requirement and 4 indicating the interventionist exceeded expectations. Concerns related to fidelity will be addressed in real time. Additionally, the on-site coordinator will complete quarterly observation checks with each interventionist to provide feedback on lesson delivery and support training for any necessary areas of improvement. The study Principal Investigator (PI) and Co-Investigator in charge of intervention training will work with the on-site project manager to provide immediate feedback, support, and booster training for interventionists if there are any concerns about fidelity adherence.

### Data monitoring and quality assurance

REDCap, hosted on secure virtual servers, provides forms for direct data entry that limit responses to appropriate data coding formats [49, 50]. REDCap also allows built-in quality checks during data collection, including range checks for entered values and warnings about questions left blank. The system also provides audit trails for tracking data entry, manipulation, import, and export. The data manager will also complete weekly data checks for quality and completeness using the REDCap data quality module to find issues with specific questions or instruments. Concerns about implementation of data collection will be addressed between the study coordinators, evaluators, and the data manager at weekly evaluation meetings.

### Safety of study participants

A Data Safety Monitoring Board (DSMB) will provide independent safety review and trial guidance during the ongoing study. Throughout the study period, the DSMB will review study processes and progress, adverse event data, and outcomes across intervention and control groups to judge whether the overall safety and feasibility of the trial remains acceptable. The DSMB may suggest appropriate courses of action to address general study safety issues which may arise. If warranted, the DSMB may recommend at any time that the entire protocol be suspended temporarily or terminated permanently. These recommendations will be directed to the study sponsor (National Institutes of Health) which has the responsibility to accept, reject or modify DSMB recommendations.

### Harms

The PI will assume responsibility of monitoring participants’ safety, including reporting any serious and unexpected Adverse Events (AEs). Any AEs will be categorized by investigators as ranging from mild to serious. Adverse Events include observed signs or participant disclosure of child abuse/neglect/domestic violence, acute substance intoxication, signs of substance abuse. Events that will be considered Serious Adverse Events (SAEs) include: any death of a study participant, a disability or incapacity which, in the opinion of the investigators, causes substantial disruption of a study participant’s ability to conduct normal life functions, hospitalization or extension of an existing hospitalization (excluding elective hospitalization for conditions unrelated to the study) and any intervention required to prevent one of the above outcomes. Serious and unexpected AEs will be reported within three business days to Johns Hopkins IRB, tribal IRBs and other tribal review entities, and the relevant NIH program officer. The PI will report actions taken by any of these groups in response to AE reports to each of the other groups in real time.

An Incidental Finding (IF) is a finding concerning an individual participant that has potential health importance and is discovered while conducting research but is beyond the aims of the study. As this is a behavioral/mental health study, most IFs that arise would be related to AEs. An IF outside of those necessitating mandatory reporting might be disclosure or discovery of a learning disability, disclosure of other risky behavior, but not immediately life-threatening (e.g., unprotected sex), disclosure of an illegal act, etc. Confidentiality will only be breached when someone is a danger to themselves or others; or they themselves are in immediate danger. Other disclosures are protected by an NIH Certificate of Confidentiality, which prevents any disclosures of participant information collected for research purposes, unless the participant provides consent for disclosure [84]. A resource card with health and mental health services will also be provided to all participants.

## Discussion

This study was designed to address the high prevalence of childhood trauma and related substance use and suicide behavior in Fort Peck Assiniboine and Sioux youth, by intervening with parents during a critical development stage for their child. Using a modular design approach [7], we selected and adapted four lessons based on content from *CETA,* four lessons based on content from *Family Spirit* and four lessons that aim to build on cultural strengths as health promotion and prevention content (i.e., the “cultural components”), which were co-created with our Tribal Advisory Board and key community leaders. The RCT with embedded SCED will allow us to simultaneously determine the effectiveness of a modular prevention program on caregiver and child outcomes and examine the added impact of specific cultural components. Our exploratory aims will allow us to examine social networks heterogeneity in overall effects, understand the relational factors that may increase both risk of suicide and opioid use and the relational characteristics of networks that act as protective factors for suicide and opioid use. Our study directly responds to the call for early trauma intervention and substance use and suicide prevention from Fort Peck Tribal Leaders and our Tribal Advisory Board.

### Limitations

There are several limitations to our study. First, most measures rely on self-report. To address this limitation, we added assessments to triangulate self-reported data, including parent and teacher reports. Second, including an active control may dilute the intervention impacts. However, community advisors stressed the importance of providing useful information to both groups, and nutrition lessons will steer clear of direct mental health promotion. Further, in low-resource settings such as the one in this study, utilizing an active control group is an ethical consideration. The control condition that was selected is both beneficial to the population—nutrition education in a community with a lack of food security and sovereignty—and for its minimal risk for confounding measure of primary and secondary intervention effects. Third, the Little Holy One curriculum has been developed through continuous consultation and advisement with a Tribal Advisory Board, resulting in lessons created for and adapted to a very specific target population. Due to this, results may have limited generalizability. That said, the other eight lessons on parenting, coping, and mental health promotion have been proven effective in their original form (before adaptation for this trial) in several other settings. Lastly, the currently planned follow-up is limited to 2 years, which may not be sufficient time to see the full impact of the intervention. Investigators plan to obtain funding in the future to follow study participants longitudinally into adolescence and young adulthood.

## Data Availability

The datasets generated and analyzed during the current study are not publicly available due to the tribal law that supports this research to respect their tribal sovereignty and confidentiality, but will be made available from the corresponding author on reasonable request in the most user-friendly, accessible, secure, and ethical format. We will take necessary steps to ensure we adhere to Fort Peck Tribal Law (Resolution #28–1744-2017) and NIH guidelines on sharing of data, in collaboration with our tribal partners.

